## 1. INTRODUCTION

### 1.1 Background

At present, China has become the country with the largest number of diabetic patients, and the disease burden of diabetes keeps increasing, especially in developing countries. Using the China Disease Surveillance System death cause monitoring and China's chronic disease and its risk factors monitoring data, it is estimated that the 2010 China Diabetes Disability Life Year (DALY), the Chinese population of diabetes per thousand people DALY value of 19.12 person-years, mainly in the residents aged 15 to 79 years, of which the highest population was 45 to 60 years old, for whom the labor force burden is higher. This result stems from the fact that diabetes increases the risk of heart disease and stroke over time. 50% of people with diabetes die from cardiovascular and cerebrovascular diseases (mainly heart disease and stroke). Foot neuropathy (nerve damage) combined with reduced blood flow increases the risk of foot ulcers, infections, and eventually amputation. Diabetic retinopathy is one of the main causes of blindness, which is the result of long-term accumulation of small blood vessels in the retina. 1% of global blindness can be attributed to diabetes. One of the main causes of kidney failure is diabetes as well. The prevalence of osteoporosis in patients with type 1 diabetes is higher than in the general population. The total risk of death is at least doubled for diabetic patients than their peers without diabetes. The risk of macrovascular, microvascular complications and death in patients with T1D was also significantly higher than in non-diabetic patients. Therefore, measures to prevent and treat diabetes are urgently needed. Adult-onset latent autoimmune diabetes (LADA) is considered to be a special phenotype of diabetes. In fact, LADA belongs to a form of T1D, which is caused by autoimmune destruction of islet  $\beta$ -cells induced by environmental factors based on genetic susceptibility background. LADA has some clinical features of T2D at onset, which is characterized by slow and latent onset, and is easily misdiagnosed as T2D due to the slow deterioration of  $\beta$ -cell function. A variety of antibodies can be detected in the serum of patients, such as glutamic acid decarboxylase antibody (GAD-Ab), protein tyrosine phosphatase ELISA (IA-2A), zinc The transporter 8 antibody (ZnT8-Ab) and the like, among which the sensitivity of GAD-Ab is the highest. T1D often combines with other autoimmune diseases, such as Hashimoto thyroiditis, Graves disease, celiac disease,

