### **Compliance evaluation of investigational medication:**

Evaluation of compliance should be based on the returned tablet count at each visit. The subjects will be asked to return all untaken investigational products and the empty packages of the taken medication.

Compliance evaluation of Saxagliptin:  $\text{actual dose taken/prescribed dose} * 100\%$

Compliance evaluation of vitamin D3:  $\text{actual dose taken/prescribed dose} * 100\%$

Participants judged to be non-compliant can continue the study if the participants understand the importance of taking their study medication as prescribed, and are willing

to comply according to prescription. If the subject continuously fail to comply, the investigator can decide whether or not to terminate participants from this study.

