## **6.6 Discontinuation of Study**

Patients may be discontinued from the study if any of the following situations occur:

- Voluntary discontinuation by the subject, revoking the informed consent;
- Safety reasons as judged by the investigator;
- Severe non-compliance to protocol as judged by the investigator;
- Incorrect enrollment, i.e. the patient does not meet the required inclusion/exclusion criteria;
- Patient lost to follow-up (as defined by, unable to reach the patient after 3 valid phone calls, fax or email, all contact should be documented in the patient's medical records);
- Pregnancy;

Investigators should record the reasons of discontinuation or drop-out subjects. Subjects need to go through relevant process and inspection of discontinuation (identical to the 26st follow-up). The random coding and research drugs of these subjects cannot be passed on to other subjects.

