### 9.2 Sample size estimation

The sample size calculations were performed based on the primary variable “absolute change in fasting C-peptide from baseline to 104-week”.

Because there is no study for the effect of Saxagliptin combined with vitamin D3 on  $\beta$ -cell function of diabetes patients, the sample size calculations in this study is based on early published literature comparing the effect of sitagliptin combining insulin and insulin therapy alone on  $\beta$ -cell function in LADA patients with the course of diabetes less than 1 year. Our study hypothesis is that saxagliptin will improve the protective effect on  $\beta$ -cell function in LADA treated with metformin (and insulin) than those with metformin (and insulin) alone, and saxagliptin combined with vitamin D will also further improve protective effect on  $\beta$  cell function in LADA treated with metformin (and insulin) than those with metformin (and insulin) alone. The means of effect of insulin treatment group and sitagliptin combining insulin group on fasting C-peptide (extent of fasting C-peptide changing from baseline to 1 year later ) which is the indication of  $\beta$ -cell function are 149.2, 108.4 individually, the standard deviations are 84.5, 52.8 individually. As twice test involved, set two-sided  $\alpha=0.025$  as significance level, and set  $\beta=0.1$  that means the power of test is 90%. According to the formula used to compare the means of two-sample:

$$n = 2 \left[ \frac{(\mu_{\alpha} + \mu_{\beta})}{\delta/\sigma} \right]^2 + \frac{1}{4} \mu_{\alpha}^2$$

Calculating with the formula and above values, we can get the sample size  $n=76$ .

According to calculation with the drop-out rate which is approximate 20%, 95 patients per group are needed. We set 100 cases per group, 300 cases in total.

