#### **9.3.1 Efficacy analysis set**

##### **Intention-to-treat (ITT) analysis**

the results of an experiment is based on the initial treatment assignment but not on the treatment eventually received. ITT analysis is intended to avoid various misleading artifacts that can arise in intervention research such as non-random attrition of participants from the study or crossover. ITT is also simpler than other forms of study design and analysis because it does not require observation of compliance status for units assigned to different treatments or comprise the incorporation of compliance into the analysis.

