### **9.4.1 Analysis of the primary variable(s)**

The primary endpoints in the study are absolute fasting C-peptide changes between saxagliptin + metformin (and insulin) group vs. metformin (and insulin) group, and vitamin D + saxagliptin + metformin (and insulin) group vs. metformin (and insulin) group from baseline after 104 weeks of treatment. The primary endpoint will be analyzed utilizing mixed model repeated measures (MMRM) on full analysis set (FAS). Within the framework of MMRM, point estimations and 2-sided 95% CIs will be presented at each visit for the mean change within each treatment group as well as the difference of the mean change between treatment groups. The following hypothesis will be tested to establish superiority:

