### **Hypothesis Testing in Superiority Trial:**

Superiority trials are designed to show a treatment effect between saxagliptin (combined with vitamin D3) + metformin (and insulin) group and metformin (and insulin) alone group. Treatment with saxagliptin (combined with vitamin D3) + metformin (and insulin) is supposed to be superior. This superiority trial can be expressed by two hypotheses:

- Null hypothesis  $H_0: \mu_S - \mu_I = 0$ , which states that there is no difference between saxagliptin (and vitamin D3) + metformin (and insulin) group and metformin (and insulin) alone group in terms of outcome variables;
- Alternate hypothesis  $H_a: \mu_S - \mu_I \neq 0$ , which states that there is a difference.

The type I error rate for each hypothesis test is adjusted to be 0.025 considering saxagliptin + metformin (and insulin) group vs. metformin (and insulin) group and saxagliptin + vitamin D3 + metformin (and insulin) group vs. metformin (and insulin) group involved.

To determine whether saxagliptin was effective, the confidence intervals for the two groups should be constructed. If the two-tailed upper limitation of 97.5% CI is less than 0, then null hypothesis  $H_0$  is rejected and a “win” declared if the absolute change of fasting C-peptide is 100 pmol/L or less in Group B in the 104 weeks. A sensitivity analysis will also be performed on the primary endpoint with last observation carried forward (LOCF) for missing values by analysis of covariance (ANCOVA). The effect of “drop-outs” (subject withdrawals), covariates (age, gender, physiologic status), and protocol violations will be analyzed by statistical models.

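### LOCF, the one named missing-data check, favours whichever arm has more or earlier drop-out on a declining endpoint, and no C-peptide is described after discontinuation

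*Protocol*

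**What the plan says.** Section 9.4.1 analyses the week-104 change in fasting C-peptide by MMRM on the full analysis set. Under its hypothesis-testing heading it adds: "A sensitivity analysis will also be performed on the primary endpoint with last observation carried forward (LOCF) for missing values", using ANCOVA. The next sentence promises that the effect of drop-outs, "covariates (age, gender, physiologic status), and protocol violations will be analyzed by statistical models", without naming a model or an assumption about the missing values.

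The endpoint is expected to decline. Section 1.1 says LADA "is easily misdiagnosed as T2D due to the slow deterioration of" beta-cell function. Section 9.2 plans on one-year changes whose means "are 149.2, 108.4 individually, the standard deviations are 84.5, 52.8 individually", and section 1.2 expects smaller changes with saxagliptin.

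On leaving the study, section 5.4 says that after continued non-compliance "the investigator can decide whether or not to terminate participants from this study". Section 6.6 lists "Severe non-compliance to protocol as judged by the investigator" among the reasons for discontinuation. Discontinued subjects have an exit visit with the content of Visit 26, including C-peptide. No later C-peptide measurement is described for them. Section 9.3.1 describes intention-to-treat as an analysis that "is based on the initial treatment assignment but not on the treatment eventually received".

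**The concern.** A sensitivity analysis for missing data should show whether the result survives a less favourable assumption than the primary one. LOCF holds a subject at the level reached at exit. On a falling endpoint this always understates that subject's week-104 loss. Whether the arm comparison shifts, and which way, depends on which arm loses more subjects or loses them sooner. Agreement between LOCF and the MMRM would naturally be read as robustness, although LOCF may itself be tilted towards the active arm.

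A second gap concerns data collection. If stopping study drug in practice means leaving the study, no week-104 value exists for those subjects. The MMRM then in effect assumes that they carried on like comparable subjects who stayed in their arm. If they lose the benefit once off drug, the effect in everyone randomised is overstated, and no later analysis can recover the missing samples.

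**Working it through.** **Inputs from the protocol (section 9.2).** Mean one-year changes 149.2 and 108.4, difference 40.8. SDs 84.5 and 52.8. Two-sided alpha 0.025, power 90%. Drop-out about 20%, not given by arm. 100 subjects per group. C-peptide is measured at screening and weeks 26, 52, 78 and 104 (section 7.1).

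**The plan's own figure.** Pooled SD = √[(84.5² + 52.8²)/2] = 70.46. The section 9.2 formula gives 74.02 + 1.26 = 75.28, rounded up to 76. Then 76/0.8 = 95, set at 100. This reproduces and is not in dispute.

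**Assumptions, not in the documents.** I read the planning means as losses in pmol/L. They are one-year values, so the 104-week loss L is ranged from 149.2 (no further loss) to 298.4 (2 × 149.2, the same rate for a second year). Decline is linear, drop-outs follow the same path as everyone else, and drop-out is 10% in control and 25% in the active arm.

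**Spurious LOCF benefit with no true effect.** A drop-out carried forward from fraction f of the follow-up is credited with f × L instead of L. The between-arm artefact is (0.25 − 0.10) × (1 − f) × L.

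| Last value | 1 − f | L = 149.2 | L = 298.4 | Share of 40.8 |
|---|---|---|---|---|
| Week 26 | 0.75 | 16.8 | 33.6 | 41% to 82% |
| Week 52 | 0.50 | 11.2 | 22.4 | 27% to 55% |
| Week 78 | 0.25 | 5.6 | 11.2 | 14% to 27% |

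Other splits, with the last value at week 52:
- 15% control, 25% active: 0.10 × 0.50 × L = 7.5 to 14.9.
- 10% control, 30% active: 0.20 × 0.50 × L = 14.9 to 29.8.
- 20% in both arms with the same timing: 0.
- More drop-out in control: the sign reverses and LOCF hides a benefit.

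In all these cases the MMRM is unbiased, because drop-outs follow the same path as those who stay.

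**No C-peptide after stopping, with a true effect.** Take 40.8 as the week-104 effect while on drug. Let 20% of active subjects stop, give no later data, and lose a share λ of the effect. The treatment-policy effect is 40.8 × (1 − 0.20λ):
- λ = 1: 32.6.
- λ = 0.5: 36.7.
- λ = 0: 40.8.

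The MMRM still estimates about 40.8, since nothing observed shows the loss. At λ = 1 the overstatement is 40.8/32.6 = 1.25, that is 25%.

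**LOCF in that second case.** With 20% drop-out in both arms, all last seen at week 26, LOCF gives 0.8 × 40.8 + 0.2 × 0.25 × 40.8 = 34.7.

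**The case against.** A reader might infer that a false claim of superiority could pass both the MMRM and the LOCF check. The documents and the arithmetic do not support that. In the no-effect case only LOCF is biased. In the second case a true effect of 32.6 remains, so the estimate is too large but superiority is not false. The decision rule in section 9.4.1 is tied to the confidence interval; nothing there gives LOCF a role in it.

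A reader might also infer that drop-out will be higher in the active arms. The protocol does not say so. Tablet counts apply only to the two saxagliptin arms, since Group A receives no investigational drug. But section 5.4 assesses metformin and insulin compliance in every arm, lets non-compliant subjects continue, and leaves termination to discretion after continued failure. The asymmetry is partial.

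Three further points stand. The exit visit includes C-peptide, so the carried value dates from exit, and placing every drop-out at week 26 is near the extreme. With equal drop-out, LOCF moves in the cautious direction (34.7 against 40.8). The intention-to-treat paragraph describes analysis by assignment and does not itself require sampling off drug, while non-compliant subjects who stay do contribute data.

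It can also be said that the choice of sensitivity analyses belongs in the SAP and that the promised statistical models may cover it. This stands only in part. The protocol itself fixes LOCF, the unnamed models commit it to nothing specific, and continued sampling has to be arranged while the trial runs.

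**Conclusion.** The point holds as a weakness of the robustness check and a gap in data collection. It is not a flaw in the primary estimate or the decision rule. LOCF depends on direction: its artefact ranges from zero to 33.6 pmol/L in favour of the active arm at the assumed 10% and 25% drop-out, and it reverses when control loses more. These sizes rest on assumed drop-out by arm, linear decline, exit timing and a 104-week loss that the protocol does not give.

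The lack of C-peptide after discontinuation could inflate the estimated effect from 32.6 to 40.8. This is an upper bound, because it takes all of the planned 20% as stopping, unobserved and fully without benefit. The amendment is worthwhile because it is cheap and its sampling part cannot be made good after the event.

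**What to change.** 1. In section 9.4.1, replace LOCF with ANCOVA by control-based multiple imputation, in which active-arm drop-outs are imputed from the control trajectory, plus a delta-adjusted tipping-point analysis around the MMRM. In the no-effect illustration control-based imputation gives no spurious difference on average, whatever the drop-out split. In the second illustration at λ = 1 it gives 0.8 × 40.8 = 32.6.
2. In sections 5.4 and 6.6, separate stopping study drug from leaving the study. Unless consent is withdrawn, keep collecting the scheduled C-peptide, at least at week 104, and include it in the full analysis set by randomised arm. The rules on when treatment stops stay as they are.

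The cost is modest programming, a short amendment, and visits that are already scheduled for about 20 subjects per arm (20% of 100).

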#### **9.4.2 Analysis of the secondary variable(s)**

The secondary endpoints including other parameters of  $\beta$ -cell function, for example C-peptide changes during MMTT. Glycaemic control parameters including HbA1c, FPG and PPG. Insulin-sparing effect is the difference of daily insulin dosage. One-way ANOVA will be used to examine the baseline data and the changes in AUC during MMTT, FPG, PPG, HbA1c and insulin dose between groups. The changes of secondary variables described above from the baseline within the same group and between groups will be analyzed with repeated measurement analysis of variance. The frequency counts

and percentages will be summarized on proportion of patients achieving  $\beta$ -cell function protection and glycaemic control.

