### **Investigational Medication:**

Saxagliptin: 5mg per pill, orally taken, 1 pill per time, once a day, taken when randomization begins

Vitamin D3: 400IU per pill, orally taken, 5 pills per time, once a day, taken after randomization

Investigational drugs should be taken at approximately the same time of a day during the study, withdrawing saxagliptin 3 days prior to Mixed-meal tolerance test (MMTT).

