### **6.2 Measurements during the study:**

- 1) Islet  $\beta$ -cell function indicators: C-peptide level of mixed-meal tolerance test at 0, 60, and 120 minutes;
- 2) Metabolic control indicators: blood glucose (0, 60, 120 minutes), HbA1c, total cholesterol (TC), low density lipoprotein-cholesterol (LDL-C), high density lipoprotein-cholesterol (HDL-C), Triglyceride (TG);
- 3) Immunological indicators: GAD-Ab;
- 4) Chronic complications indicators: electrocardiogram (ECG), Color Doppler Ultrasound of carotid artery, vertebral artery, and lower extremities arteries,

fundus examination and photography, urinary albumin-to-creatinine ratio (UACR), renal function (calculate the estimated glomerular filtration rate, eGFR), electroneuromyography, bone mineral density;

- 5) Drug safety assessment indicators: complete blood count, aspartate aminotransferase (AST), alanine transaminase (ALT), total bilirubin (TBIL), direct bilirubin (DBIL), serum albumin (ALB), Blood Urea Nitrogen (BUN), creatinine (Cr), uric acid (UA), blood electrolyte, serum 25(OH)D, 24-hour urinary calcium and phosphate, B-ultrasound of the urinary system, and urine pregnancy test;
- 6) Gene analysis: HLA-DQ, -DR, and vitamin D receptor (VDR) gene polymorphism and immune repertoire polymorphism.

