**6.4.7 Visit 8 (Week 26  $\pm$ 1week) 【outpatient visit】**

- Check for discontinuation of the study
- Physical examination
- Collection/distribution of patient diary
- Adjustment of basic medication
- Counting/retrieval of investigational medication
- Dispensation of investigational medication
- Record past/ concomitant medication
- Evaluation of compliance
- MMTT test 0, 60, 120 min blood glucose (conduct at each study site); 0, 60, 120 min C-peptide (deliver to central laboratory)
- 25(OH)D test, gene analysis (deliver to the central laboratory)

- HbA1c, blood routine test, blood biochemical, blood electrolyte, urine pregnancy test, 24-hour urine calcium and phosphate
- 12-lead ECG
- BUS of urinary system
- Record adverse events

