### **7.1 Efficacy assessments**

- C-peptide: they were tested in a central laboratory. Detection was carried out by chemiluminescence using a commercially available kit (Adiva Centaur System, Siemens, Germany). The intra- and inter-assay variation coefficients were 3.7-4.1% and 1.0-3.3% respectively. Fasting serum C-peptide, peak C-peptide (60 minutes) and the area under curve of the 120-minute C-peptide were measured using a mixed meal tolerance test (MMTT, as follows). Detection is performed at V1, V8, V14, V20, and V26.
- HbA1c: it was tested in local medical center laboratories independently. The measurements are performed at V1, V5, V8, V14, V20, and V26.
- MMTT: participants will be provided with instant noodles with the net weight of 75g, and without any condiment oil. Timing of the 1-hour and 2-hour postprandial tests starts from the beginning of the meal. Participants will be required to finish the meal in 15 minutes once started. Three days before the MMTT, the participants must be reminded to assure at least 150 grams of carbohydrate intake every day. Before visiting, the participants must have fasted for at least 8 hours and abstained from tobacco, alcohol and caffeine for at least 24 hours. Confirm that the patient did not take saxagliptin 3 days before visit, and did not take the insulin injection in the morning of the visit date.

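### Section 9.4.2 counts FPG and PPG as glycaemic control, but their scheduled post-baseline values are taken after a 3-day saxagliptin stop

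*Protocol*

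**What the plan says.** Section 9.4.2 names three glycaemic control variables, "Glycaemic control parameters including HbA1c, FPG and PPG", and applies one-way ANOVA to "the changes in AUC during MMTT, FPG, PPG, HbA1c and insulin dose between groups", with repeated-measures ANOVA as well. Section 9.4.4 repeats the one-way ANOVA for the exploratory comparison.

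The treatment section (5.2) calls for "withdrawing saxagliptin 3 days prior to Mixed-meal tolerance test (MMTT". The MMTT procedure in section 7.1 has the site check this at the visit: "Confirm that the patient did not take saxagliptin 3 days before visit". It also has the site check that the patient "did not take the insulin injection in the morning of the visit date", with no arm exempted.

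The visit lists place site glucose inside the meal test: "MMTT test 0, 60, 120 min blood glucose (conduct at each study site" appears at Visit 8, and the same item recurs at Visits 14, 20 and 26. Section 6.2 describes "Metabolic control indicators: blood glucose (0, 60, 120 minutes), HbA1c" and names no other glucose sample. In section 2.2 the glycaemic outcomes are change in HbA1c and the proportion with HbA1c below 7%. FPG and PPG are not on that list.

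**The concern.** Stopping saxagliptin before the meal test suits C-peptide as a measure of beta-cell function, because the drug's immediate action is meant to be out of the way. The same samples are then used for a different question, namely how well glucose is controlled on treatment. In Groups B and C the add-on drug has been removed for 3 days. In Group A there is nothing to remove.

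What is at stake is interpretation. A flat FPG or PPG comparison could be read as showing that saxagliptin adds nothing to glycaemic control, although the samples were not taken under the treatment being judged. The protocol's own benefit/risk section (1.3) reports that saxagliptin lowered FPG and PPG in earlier trials, so the planned test looks for a known effect under conditions that remove some or all of its acute part.

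**Working it through.** **Is there another scheduled source of FPG or PPG?**

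- Section 6.2 and Appendix C, section 1 (test items): glucose at 0, 60 and 120 minutes only.
- Visits 8, 14, 20 and 26 (weeks 26, 52, 78 and 104): these samples are part of the MMTT.
- Table 1, note 4: the biochemistry panel is lipids, liver and renal function, without glucose.
- Section 7.2.1: blood glucose is named as a site test, but no separate draw is scheduled.
- Abbreviations: FPG is a plasma value, so meter readings do not supply it by default.
- Section 6.1 and Table 1: self-monitored glucose (SMBG) is kept in the diary and listed under efficacy evaluation. No text makes it the source of FPG or PPG.

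On the text as it stands, all four post-baseline time points come from the meal test.

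**What is withheld, and from whom?**

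| Treatment | Group A | Groups B and C |
|---|---|---|
| Saxagliptin | not given | stopped for 3 days |
| Morning insulin | withheld | withheld |
| Metformin | not withheld | not withheld |
| Vitamin D3 | not given | not withheld (Group C only) |

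Only the saxagliptin stop differs between arms when B or C is compared with A. When C is compared with B, both stop it.

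**Baseline.** Visit 1 falls in weeks -6 to 0, and exclusion criterion 4 bars DPP-IV inhibitors in the 8 weeks before randomization. Baseline is therefore saxagliptin-free as well. The change in FPG or PPG runs from one saxagliptin-free state to another, and no time point captures the effect on drug.

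**Size.** The protocol gives no FPG or PPG effect, SD or power. Its only calculation, 76 per group for fasting C-peptide, reproduces: 75.28 rounds up to 76, and 76/0.8 = 95. It says nothing about glucose. What follows is illustration only.

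Assume n = 80 evaluable per arm (100 less 20% drop-out), two-sided alpha 0.05, an on-drug effect of e SD, and a fraction f of it lost through the stop:

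power = Φ( e(1 − f)·√(n/2) − 1.96 )

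For e = 0.45 and f = 0.5: 0.225 × 6.325 − 1.96 = −0.537, so power is 30%.

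| On-drug effect e | f = 0 | 25% | 50% | 75% | 100% |
|---|---|---|---|---|---|
| 0.30 SD | 48% | 30% | 16% | 7% | 2.5% |
| 0.45 SD | 81% | 57% | 30% | 11% | 2.5% |
| 0.60 SD | 97% | 81% | 48% | 16% | 2.5% |

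At 100% loss only the one-directional error rate remains. Neither e nor f can be taken from the protocol.

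**HbA1c.** Between MMTT visits 26 weeks apart, the stop covers 3 of 182 days, or 1.6%. HbA1c is little affected.

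**The case against.** **The stop is deliberate, and source rules belong in the SAP.** The first part is right, and nothing here asks to change the stop. The second stands in part: how FPG and PPG are derived and how SMBG is summarised can be left to the SAP, so the lack of an SMBG analysis is no fault of this document. But the protocol itself has already fixed the variables, their label and the test, and the label does not fit the conditions of sampling.

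**No listed endpoint is touched.** This stands. FPG and PPG appear in neither the secondary nor the exploratory outcome lists, no decision rule uses them, and the HbA1c result would be reported beside them. It limits the weight of the point.

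**The direction is not certain.** This also stands. A reader might infer a fixed bias towards no effect, or a stated share of the effect lost. The documents support neither. They say nothing about how quickly the glucose effect wanes. Insulin is adjusted individually in an open-label trial (section 5.2); if it was titrated lower in Groups B and C, the off-drug difference could pass zero. If saxagliptin preserves beta cells, as section 1.2 supposes, some difference would remain off drug.

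**Section 9.4.4.** A reader might extend the asymmetry to it. Its analyses are mainly saxagliptin plus vitamin D3 against saxagliptin, and both groups stop the drug, so the one-sided problem does not apply there.

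**Morning insulin.** Withholding it applies to every arm and is not in itself a one-sided error.

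**Conclusion.** The point holds as a matter of labelling and interpretation. At all four post-baseline time points, FPG and PPG in Groups B and C are off-saxagliptin values. In the comparisons of B with A and of C with A they cannot be read as on-treatment glycaemic control. Attenuation is to be expected, because the drug's acute effect is removed in the treated arms only, but its size cannot be derived from the protocol and differing insulin titration could alter it. The conclusion rests on the MMTT being the source of FPG and PPG, which is the only reading the visit schedule supports unless the SAP names another.

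In the comparison of C with B only the label is wrong. HbA1c remains a sound measure of glycaemic control. The point is minor, but as written the plan invites a predictable misreading.

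**What to change.** Reconcile section 9.4.2 with sections 5.2 and 7.1 by wording alone, leaving the saxagliptin stop as it is:

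- In section 9.4.2, report MMTT glucose as measured after the saxagliptin stop, alongside MMTT C-peptide, and take it out of the glycaemic control parameters. Use the same label in section 9.4.4.
- Base conclusions on glycaemic control on HbA1c (change from baseline and the proportion below 7%), in line with section 2.2.
- Use diary SMBG at most as supportive description. The protocol sets no times, no frequency and no fasting or post-meal split for it, so it is not a ready replacement for FPG and PPG. It is also self-recorded in an open-label trial.

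No new data are needed. The cost is that FPG and PPG no longer count as evidence on glycaemic control.
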